#### Randomisation

We used a stratified random sampling by disease (HF, CLD or both), which consisted of the random selection of patients for allocation to the control and intervention groups from three containers holding the codes of the initial patients. Subsequent draws were made to maintain the 1:1 ratio between the two study groups and between the three different strata considered.

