### Study variables

#### Initial assessment and baseline data

The following *socio-demographic data *will be collected for every patient taking part in the study: health centre, assigned GP and nurse, date of birth and age, gender, living arrangements, main caregiver and relationship with the caregiver, level of education and the existence of any adverse social factors (*i.e*.: poverty, social exclusion, loneliness, lack of support, isolation, recent widowhood).

The following *clinical variables *will also be recorded: main disease (HF and/or CLD), degree of severity of the disease (based on the FEV1 - forced expiratory volume in one second- for COPD and on the NYHA - New York Heart Association- classification and the ejection fraction for HF. Severity of illness measures will be collected at the moment of enrolment from the clinical records depending on availability and will be used to ensure comparability between the two groups), requirement for home oxygen therapy, name and list of the drugs taken regularly, adherence to the prescribed medication (compliance) using the four-item self reported scale proposed by Morinsky *et al. *[21], the Barthel Index (BI) [22], the EuroQol questionnaire (EQ-5D) [23-25], and the Zarit Burden Interview (ZBI) [26-28].

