##### 1. Primary outcome measure

*Number of hospital admissions due to any cause that occurred in a period of 12 months post-randomisation*.

The hospitalizations will be classified as due to HF, due to CLD (*i.e*., COPD, asthma and other respiratory conditions) and non-cardiorespiratory causes.

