#### Description of the baseline characteristics of the patients

The unit of the study is the patient. The following statistics will be used for the descriptive analysis: mean, standard deviation, median and rank for the quantitative variables, and frequency and percentage for the qualitative variables. Socio-demographic and baseline clinical data will be compared between the two groups in order to test the homogeneity. Losses occurring during the study will be analysed and the main baseline characteristics of dropouts will be compared to those who have completed the study. For the comparison of quantitative variables, the Student's t-test and the non-parametric Mann Whitney U test will be used for normally and non-normally distributed data, respectively. The Chi-square or the Fisher's exact tests will be used for the comparison of qualitative variables. The level of statistical significance will be set at p < 0.05.

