#### Analysis of the main outcome measure and impact on the use of the health care services

Firstly, at 3, 6 and 12 months follow-up, a descriptive analysis of the primary and secondary outcome measures will be carried out in the two study groups (number of hospital admissions, duration of the hospital stay and mortality rate). The variables related to the use of health care services, clinical efficacy, functional status of the patients (BI), the health related quality of life -HRQL- (EQ-5D) and the family/caregiver burden (ZBI) will also be analysed. Additionally, given that certain variables will have different follow-up periods, the incidence-rates of certain variables, such as mortality, hospital admissions, visits and episodes of worsening will be calculated.

Subsequently, both primary and secondary outcome measures will be compared between the two groups of patients at each follow-up point to test whether significant differences exist. Any changes in the functional condition (BI) or HRQL of the patients (EQ-5D) and caregiver burden (ZBI) with respect to the baseline levels will also be assessed at 3, 6 and 12 months (*i.e*., difference between the follow-up and initial scores). Quantitative variables will be compared using the Student t-test or the non-parametric Mann Whitney U test, while qualitative variables will be assessed using the Chi-Square or Fisher's exact tests. The Student's paired t-test will be used to compare the differences between the baseline scores on the BI, the EQ-5D and the ZBI and the scores obtained at 3, 6 and 12 months follow-up, for each group of patients.

If statistically significant differences are detected between the CG and the IG for the baseline characteristics analysed, the comparisons of the main outcome measures will be adjusted by the corresponding baseline variables. A logistic regression model will be used to compare dichotomous categorical variables (such as, mortality), while a general linear model will be used for quantitative variables (such as, the duration of hospital stay). In the latter case, the dependant variable will be appropriately transformed if it does not fit the normal distribution. Finally, multilevel analysis will be performed to test the effect of the individual primary care professionals involved and the clinical practice site on the results.

Whenever possible, the number needed to treat (NNT) will be calculated for the primary outcome variable (number of hospital admissions).

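### Allocation is stratified by disease, but the outcome comparisons leave the stratum out and the adjustment rule is very unlikely to bring it in, so available precision may be given up

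*Protocol article*

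**What the plan says.** Under Randomisation, the protocol article states: "We used a stratified random sampling by disease (HF, CLD or both". It adds: "Subsequent draws were made to maintain the 1:1 ratio between the two study groups and between the three different strata considered". Disease category is also among the clinical variables recorded at baseline.

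The primary outcome is "Number of hospital admissions due to any cause that occurred in a period of 12 months post-randomisation".

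Under Analysis of the main outcome measure and impact on the use of the health care services, the between-arm comparisons are named. For measured and counted outcomes, admissions among them, the text reads: "Quantitative variables will be compared using the Student t-test or the non-parametric Mann Whitney U test". For categorical outcomes such as death, chi-square or Fisher tests are named. None of these tests uses the strata.

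The same section makes adjustment conditional: "If statistically significant differences are detected between the CG and the IG for the baseline characteristics analysed". In that event the main comparisons are adjusted for the variables concerned, by logistic regression or a general linear model. The screening step is under Description of the baseline characteristics of the patients: "Socio-demographic and baseline clinical data will be compared between the two groups in order to test the homogeneity", at p < 0.05.

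Two other models are described. The multilevel analysis concerns individual professionals and practice site. The QALY regression, under Assessment of the effectiveness, controls for baseline utility. Neither names disease.

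**The concern.** Stratified allocation removes between-stratum variation from the true sampling variance of the arm difference. An unstratified test does not recognise this: it leaves that variation in its error term. If the strata differ in admission rate, the test's standard error is too large, its confidence interval too wide and its true size below 5%.

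The adjustment rule does not repair this. It selects covariates by imbalance, and a stratification factor is the variable for which the design has arranged balance. The choice of tests and the rule therefore work together to leave out the one factor that the sponsor chose to stratify on.

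What is at stake is efficiency. Recruitment is capped by the number of devices and eligible patients, and the stated power is 72%, so better use of the existing design is one of the few ways to gain precision.

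**Working it through.** **Inputs from the document (Sample size).** 30 per arm with 10% loss gives 27 per arm. Control mean 3.5 with a 35% reduction gives a difference of 0.35 × 3.5 = 1.225. SD 1.7, alpha 5%. Two-sided testing is assumed, since sidedness is not stated.

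**Step 1: the plan's own figure.** SE = 1.7 × √(2/27) = 0.463, and the noncentrality is 1.225 / 0.463 = 2.65. The noncentral t on 52 degrees of freedom gives 73.8% power. Allowing for a Mann-Whitney efficiency of 0.955 gives 71.8%. Both are close to the stated 72%, so that figure is consistent with an unstratified calculation.

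**Step 2: can the adjustment rule select disease?** Chi-square test of disease by arm, with about 60 patients:

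| Stratum counts, one arm v the other | p |
|---|---|
| 10/10/10 v 10/10/10 | 1.00 |
| 11/10/9 v 9/10/11 | 0.82 |
| 14/8/8 v 8/14/8 | 0.19 |
| 15/8/7 v 7/8/15 | 0.055 |

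If stratum counts differ by at most one between arms, the smallest p found over all such tables with 58 to 62 patients is 0.37. The rule does not fire for disease unless balance is badly broken.

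**Step 3: what the omission costs.** Let R² be the share of within-arm variance explained by disease stratum. The document gives no value, so 0 to 20% is an assumed range.

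- True SE under balanced strata: 1.7 × √(1 − R²) × √(2/27).
- SE that the unadjusted test uses: about 1.7 × √(2/27) = 0.463, whatever R² is.
- Adjusted power: noncentral t with the true SE and 54 − 4 = 50 degrees of freedom.

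The unadjusted test was simulated with 100,000 trials per scenario, a normal outcome and three equal strata of 9 per arm (also an assumption).

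| R² | True SE | Noncentrality, adjusted | Unadjusted size | Unadjusted power | Adjusted power | Change (points) |
|---|---|---|---|---|---|---|
| 0% | 0.463 | 2.65 | 5.0% | 74.0% | 73.8% | about 0 |
| 5% | 0.451 | 2.72 | 4.4% | 74.3% | 75.9% | +1.6 |
| 10% | 0.439 | 2.79 | 3.8% | 74.7% | 78.1% | +3.4 |
| 20% | 0.414 | 2.96 | 2.9% | 75.9% | 82.7% | +6.8 |

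The size of the adjusted test stayed between 4.9 and 5.1%. At R² = 20% the adjusted standard error is 1 − √0.8, or about 11%, smaller.

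**Step 4: sensitivity to stratum sizes.** With assumed strata of 11/9/7 per arm and 20,000 trials, power was 74.0 v 75.6% at R² = 5%, 74.9 v 78.4% at 10% and 76.1 v 83.0% at 20%. The gains are essentially the same.

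**Step 5: the rank test.** The unstratified Mann-Whitney test in the same equal-strata simulation (20,000 trials) had power of 71.3, 71.9, 71.6 and 72.8% at R² = 0, 5, 10 and 20%, and size of 4.9, 4.4, 3.8 and 2.6%. The pattern is the same.

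**The case against.** **The planned analysis delivers what the protocol promises.** Under its own inputs, the unadjusted t-test keeps 74 to 76% power across the range and the Mann-Whitney test about 71 to 73%, against a stated 72%. This stands. A reader might infer that the trial falls short of its stated power. It does not: what is forgone is a gain.

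**The error is in the safe direction.** The estimate is unbiased under balanced allocation and the true size is at or below 5%. This stands too. Nothing here makes a false positive more likely.

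**The size is unknown and may be small.** No admission rates by disease are given. Every patient is on home care with at least two admissions in the previous year, and the outcome is all-cause, which may narrow differences between strata. At R² of 5% or less the gain is under 2 points. This stands, and is why only a range can be given.

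**More dramatic figures can be produced.** Poisson counts with control stratum means 2.5/3.0/5.7 (weights 11/9/7) give roughly 60% v 74% power. But the control-arm variance is then 3.50 + 1.75 = 5.24 (unrounded components), so the SD is 2.29 rather than 1.7, and strata explain 33%. The low 60% partly reflects the larger variance and cannot be read as a loss from the plan's 72%.

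**Disease is not strictly barred from adjustment.** Draws were made from the codes of the initial patients, consent is described separately, and losses are foreseen. Refusals or losses could unbalance the strata enough to trigger the rule. This is possible but unlikely: even 15/8/7 v 7/8/15 gives p = 0.055.

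**The article is condensed.** It does not list every covariate of the multilevel and QALY models, so those models are silent on disease and do not exclude it. That does not reach the main point, because the article itself names the tests and fixes the adjustment rule for the main comparison.

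**Conclusion.** The point holds as a matter of efficiency. The design stratifies by disease, the named tests ignore the strata, and the conditional rule is very unlikely to select disease while within-stratum balance is kept. If disease is prognostic, the primary test is conservative and its interval wider than it needs to be.

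For R² of 5 to 20% the forgone power is about 2 to 7 points; for R² near zero it is nil. These figures rest on the plan's difference and SD, 27 per arm, two-sided 5% testing, a normal outcome, near-exact balance within strata and an assumed R². The document does not support a claim of bias, of an inflated error rate or of power below the stated 72%. The case for changing the plan is that the possible gain is useful in a trial whose size is capped, while the cost is close to nothing.

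**What to change.** In the section on analysis of the main outcome measure, state that:

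- Disease stratum (three levels: HF, CLD, both) is a prespecified fixed factor in the primary comparison of admissions, whatever the baseline p-values.
- The same factor enters the models for the other quantitative outcomes.
- If a rank test is kept, its stratified (van Elteren) version is used.
- For binary outcomes such as mortality, a stratum-adjusted method is used where event numbers allow. With about 60 patients, events may be too sparse, and the calculations above do not cover that case.

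The cost is wording, 2 degrees of freedom, and about 0.1 point of power if disease proves not to be prognostic. The stratum is already recorded at baseline, and general linear and logistic models are already planned, so no new data or model type is needed.

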##### Assessment of the effectiveness

The QALYs, calculated from the EQ-5D questionnaire results, will be used as a measure of effectiveness. The QALYs will be estimated by calculating the area under the curve (AUC), which is obtained by summing up the areas of the geometrical shapes obtained by linear interpolation between the utility scores during the study period [35]. In addition, the baseline utility will be controlled using a regression-based adjustment, since there tends to be a strong correlation between the baseline utility of patients and the QALY scores [35].

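### EQ-5D, Barthel and Zarit: between-arm tests are valid but adjusted for baseline only after a significant baseline test, and within-arm paired t-tests are added that do not compare treatments

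*Protocol article*

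**What the plan says.** Four provisions bear on the three scales. The first three are in the protocol article's section on analysis of the main outcome measure and use of health care services.

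- **Between-arm comparison.** The plan states that "both primary and secondary outcome measures will be compared between the two groups of patients at each follow-up point". The method is that "Quantitative variables will be compared using the Student t-test or the non-parametric Mann Whitney U test". Change on the three scales, defined as the "difference between the follow-up and initial scores", is also to be assessed at 3, 6 and 12 months. No baseline covariate enters these tests.
- **Within-arm tests.** "The Student's paired t-test will be used to compare the differences between the baseline scores on the BI, the EQ-5D and the ZBI" with "the scores obtained at 3, 6 and 12 months follow-up, for each group of patients". Each arm is therefore tested on its own.
- **Conditional adjustment.** "If statistically significant differences are detected between the CG and the IG for the baseline characteristics analysed", then "the comparisons of the main outcome measures will be adjusted by the corresponding baseline variables", using a general linear model for quantitative variables.
- **QALYs.** Under Assessment of the effectiveness, "the baseline utility will be controlled using a regression-based adjustment". No condition is attached, and the reason given is the usual strong correlation between baseline utility and QALYs.

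Baseline values of all three scales are collected (Initial assessment and baseline data).

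**The concern.** There are two separate issues.

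**Precision.** A baseline score usually predicts the follow-up score on the same scale. Using it as a covariate gives a between-arm estimate with, in large samples, no more variance than a comparison of raw follow-up scores or of change scores. The plan has the data and uses this approach for QALYs, but for the scales it makes adjustment depend on a chance finding at baseline. Recruitment is held at 30 per arm by devices and eligible patients, so precision cannot be bought with more patients.

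**Interpretation.** A paired test within one arm asks whether that arm changed. It does not ask whether telemonitoring made a difference, which is what the objectives ask. Eighteen such tests (3 scales x 3 visits x 2 arms, counting one score per scale) will produce patterns in which one arm is significant and the other is not. A reader can easily take such a pattern for a treatment effect.

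**Working it through.** **Plan's own figure.** The only power stated is 72%, for admissions. The inputs are 30 per arm less 10% = 27; difference 0.35 x 3.5 = 1.225; SD 1.7; 5% level, taken as two-sided. The noncentrality is 1.225 / (1.7 x sqrt(2/27)) = 2.65, which gives 73.8% by the t-test. This agrees with 72% to within 2 points. It concerns another outcome and does not bear on this point. No SD, correlation or power is given for the three scales.

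**How often would adjustment be triggered?** Under randomisation, a test at p < 0.05 on a given baseline score is significant in about 5% of trials. The trigger depends on chance imbalance and not on how well the score predicts outcome.

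**Precision.** Assume equal SDs at baseline and follow-up and a correlation rho between them (not in the documents, so shown as a range). The large-sample variance of the between-arm difference, in units of the raw follow-up variance, is:

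- raw follow-up score: 1
- change score: 2(1 - rho)
- ANCOVA: 1 - rho^2

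Relative to ANCOVA, the change score is therefore 2/(1 + rho) and the raw score is 1/(1 - rho^2).

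| rho | change / ANCOVA | raw / ANCOVA | patients per arm that a change-score analysis needs to match ANCOVA with 27 |
|---|---|---|---|
| 0.3 | 1.54 | 1.10 | 27 x 1.54 = 42 |
| 0.5 | 1.33 | 1.33 | 27 x 1.33 = 36 |
| 0.7 | 1.18 | 1.96 | 27 x 1.18 = 32 |
| 0.9 | 1.05 | 5.26 | 27 x 1.05 = 28 |

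The 27 is borrowed from the sample-size section. The two unadjusted analyses fail at opposite ends: change scores lose most when rho is low, raw scores when rho is high.

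**Within-arm tests.** Suppose both arms change by the same amount, so that there is no treatment effect. If each paired test is significant with probability p, exactly one arm is significant with probability 2p(1 - p), and the telemonitoring arm alone with probability p(1 - p). With 27 per arm and p from the noncentral t distribution:

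| common change (in SDs of change) | p | exactly one arm | telemonitoring arm only |
|---|---|---|---|
| 0 | 0.05 | 9.5% | 4.7% |
| 0.2 | 0.17 | 28% | 14% |
| 0.3 | 0.32 | 44% | 22% |
| 0.4 | 0.52 | 50% | 25% |
| 0.6 | 0.85 | 25% | 13% |
| 0.8 | 0.98 | 4% | 2% |

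The maximum is at p = 0.5: 2 x 0.5 x 0.5 = 50%, half of it in each direction. These are probabilities per scale and visit. A simulation of 20,000 trials per setting agreed: at rho 0.5, 9.6% with no change and 50.2% with a common change of 0.4. In the same simulations, with correlations of 0.5 and 0.7, the between-arm t-test on change scores was significant in 4.6% to 5.1% of trials.

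**The case against.** The strongest reply is that the plan already compares the arms and that this comparison is valid. That stands. In a randomised trial, a t-test on follow-up or change scores is unbiased and keeps its error rate. A reader might infer that the paired tests take the place of a between-arm comparison, or that the investigators will claim an effect when only the telemonitoring arm is significant. The text supports neither reading: the paired tests are additional, and nothing says what will be concluded from them.

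Second, the plan does contain a baseline adjustment. That also stands, but it is conditional. Its reach is unclear as well. The examples given for it, mortality and duration of stay, are secondary outcomes in Table 2, so the wording is not confined to the primary outcome; whether it extends to the three scales is not said.

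Third, the sizes rest on assumptions. Neither rho nor the power of the paired tests is in the documents. The correlation mentioned for QALYs is between baseline utility and QALYs, which include the baseline value as the start of the area, so it does not fix rho for the scales. The loss from change scores is small if rho is high. The figures near 50% are the top of the range, not a typical value, and the nine scale-visit combinations are correlated and cannot be treated as nine independent chances.

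Fourth, one might argue that regression to the mean will make within-arm changes significant because patients enter after repeated admissions. The documents do not show this. Patients are selected on admissions, diagnosis and home-care status, not on their EQ-5D, Barthel or Zarit scores.

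**Conclusion.** The point holds in limited form, for secondary outcomes. The between-arm comparisons of the three scales are valid but needlessly imprecise, because baseline adjustment is tied to a significance test that will seldom trigger it and may not cover these scales. This is out of step with the unconditional adjustment of QALYs built from the same EQ-5D. Under equal SDs and rho of 0.3 to 0.9, the excess variance over ANCOVA is 54% down to 5% for change scores and 10% up to 426% for raw follow-up scores.

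The within-arm tests add no treatment comparison. With no arm difference they disagree in 9.5% of trials if neither arm changes and in at most 50% per scale and visit; significance in the telemonitoring arm alone is at most 25%. They invite a misreading, but the plan does not commit to it. The primary conclusion and the type I error of the between-arm tests are unaffected.

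**What to change.** For each of the three scales:

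1. Pre-specify one between-arm model: ANCOVA at 12 months, or a mixed model over 3, 6 and 12 months. Include the baseline score and the disease stratum used in randomisation as covariates, regardless of any baseline test.
2. Report the adjusted difference between arms with its 95% confidence interval.
3. Keep a rank-based or bootstrap check, since the scores are bounded and may be skewed. This replaces the Mann-Whitney route that the present plan offers.
4. Drop the within-arm paired t-tests and show within-arm change descriptively.

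The cost is mainly wording. The baseline scores are already collected, the planned general linear model already provides ANCOVA, and the covariates use only a few degrees of freedom. The change does not by itself settle how patients who die are handled on these scales; the Study variables section expects deaths among the losses, and the chosen model should say how it treats them.

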### Sample size

Thirty patients will be recruited in each of the study groups, the main constraints being the number of available devices and the number of potential patients fulfilling the inclusion criteria in the Bilbao Primary Care Health Region. Thus, if 30 patients are included in each group, and a 10% loss to follow-up is assumed at 12 months (based on previous analysis of mortality and other causes of loss in patients with similar characteristics), we have estimated a statistical power of 72% to detect significant differences between the CG and the IG in the mean number of total admissions with a level of significance of 5%. For the power calculation, it has been assumed that the mean number of admissions in the CG is 3.5, the standard deviation 1.7, and there will be a 35% decrease of hospitalisations in the IG with respect to the CG [32-34]. The power calculations have been performed with the sample size calculation software Ene 2.0.

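### The main comparison is adjusted only for baseline variables that test significant, and the disease strata used for randomisation are left out: the estimator is not fixed in advance and precision is lost

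*Protocol article*

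**What the plan says.** Three parts of the protocol article bear on this.

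- **Randomisation.** "We used a stratified random sampling by disease (HF, CLD or both"), with later draws made to keep the arms 1:1 within the strata.
- **Description of the baseline characteristics of the patients.** "Socio-demographic and baseline clinical data will be compared between the two groups in order to test the homogeneity", using t, Mann-Whitney, chi-square or Fisher tests at p < 0.05.
- **Analysis of the main outcome measure and impact on the use of the health care services.** Quantitative outcomes, which include the number of admissions, are compared by t-test or Mann-Whitney test. Then: "If statistically significant differences are detected between the CG and the IG for the baseline characteristics analysed", the main comparisons are adjusted for the variables concerned, with a general linear model for quantitative outcomes. A multilevel analysis looks at professional and practice site. Disease stratum is named in none of these analyses.

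By contrast, the section on assessment of effectiveness adjusts QALYs for baseline utility in every case, on the ground that baseline utility correlates with the outcome.

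**The concern.** Under proper randomisation, a significant baseline difference is a chance event. Whether a covariate belongs in the model depends on how well it predicts admissions, and a baseline p-value does not measure that. With about 30 patients per arm, the test will flag irrelevant variables by chance and pass over prognostic ones.

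The rule also works against the design. Disease was chosen as the stratification factor and is held at 1:1 within strata, so it should seldom differ significantly between arms and will seldom be adjusted for. If disease predicts admissions, a test that ignores it has a standard error that is too large.

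This matters because the sample size is capped by the number of devices and of eligible patients, and the stated power is only 72%. Covariate adjustment is one of the few ways left to gain precision without more patients.

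**Working it through.** **Inputs (Sample size section).** "Thirty patients will be recruited in each of the study groups"; a 10% loss leaves 30 × 0.9 = 27 per arm. "it has been assumed that the mean number of admissions in the CG is 3.5, the standard deviation 1.7"; "there will be a 35% decrease of hospitalisations in the IG with respect to the CG". The difference is 0.35 × 3.5 = 1.225 admissions, or 1.225/1.7 = 0.72 SD. The significance level is 5%, taken as two-sided because the protocol does not say.

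**1. The protocol's own figure.** It reports: "we have estimated a statistical power of 72% to detect significant differences between the CG and the IG".
- Standard error = 1.7 × √(2/27) = 0.463; noncentrality = 1.225/0.463 = 2.65.
- Noncentral t on 52 df: power 73.8%.
- Same calculation with the Mann-Whitney efficiency factor (27 × 0.955 = 25.8 per arm): 71.8%.

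The stated 72% is reproduced.

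**2. How often the rule changes the model when randomisation is sound.** With k independent tests at 5%, P(at least one flag) = 1 − 0.95^k.

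| k | P(at least one flag) |
|---|---|
| 5 | 22.6% |
| 10 | 40.1% |
| 15 | 53.7% |
| 20 | 64.2% |

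The protocol fixes no number of tests, and its baseline variables will be correlated, so k and independence are assumptions.

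**3. Power of a fixed adjusted model.** Residual SD = 1.7 × √(1 − R²); df = 54 − 2 − 3 = 49 (two stratum terms and one further covariate). The documents give no R², so a range is shown.

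| Assumed R² | Power |
|---|---|
| 0 | 73.7% |
| 0.05 | 75.9% |
| 0.10 | 78.1% |
| 0.20 | 82.7% |

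Against 73.8% unadjusted, the cost if the covariates explain nothing is about 0.1 point. This formula treats the covariates as balanced between arms, which suits the stratum.

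**4. Simulation of the rule.** 8,000 trials per scenario, 27 per arm, three equal strata balanced 9/9, ten independent baseline covariates of which at most one is prognostic. The first two columns assume R² of 0.10 for stratum and 0.20 for the prognostic covariate.

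| Analysis | Null rejection | Power | Power if nothing is prognostic |
|---|---|---|---|
| Plain t-test | 4.0% | 75.2% | 75.0% |
| Protocol's conditional rule | 3.5% | 73.8% | 72.2% |
| Stratum always | 5.0% | 78.0% | 74.9% |
| Stratum and covariate always | 5.0% | 86.4% | 74.0% |

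The simulation error is about 0.5 point for power and 0.2 point for null rejection. Over all five scenarios run, null rejection was 4.0 to 5.1% for the t-test and 3.5 to 5.1% for the conditional rule. The last column shows that always adjusting for stratum costs 0.1 point at worst, and that adding a covariate of no value costs about 1 point (75.0% to 74.0%).

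**The case against.** The strongest defence is that nothing here makes the trial invalid. The unadjusted comparison is unbiased over randomisation, and its standard error already allows for chance imbalance. The rule is written down in advance, is mechanical, looks at baseline data rather than outcomes, and is applied by analysts blinded to allocation. The simulated test is, if anything, conservative. All of this stands.

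Three stronger readings are therefore tempting but unsupported:

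- **That the rule biases the result or inflates false positives.** One can construct an unlucky imbalance just short of significance and compute the shift it leaves in the estimate. That describes one draw, not the expected error, and the simulated null rejection does not exceed the nominal level beyond simulation error.
- **That the model is picked after seeing outcomes.** The trigger uses baseline data only. What is true is narrower: the model cannot be named until the baseline p-values are known. The text also does not say outright whether an adjusted result replaces the unadjusted one, so precedence is open as well.
- **That prior-year admissions are already in the dataset and subject to the rule.** The baseline list under Initial assessment and baseline data does not contain them. The eligibility and selection sections document only a threshold of two or more, and later patients are sought through health-centre meetings. That a count can be retrieved from hospital records is likely but is an inference.

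It may also be said that a condensed article can leave the stratum term to an analysis plan. That would answer silence. Here the article itself states the default test and the only route by which a covariate enters, and that route tends to shut disease out. The gain from stratum alone may be small: about 3 points at an assumed R² of 0.10.

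**Conclusion.** The point holds as one of precision and pre-specification. The protocol adjusts the main comparison according to chance baseline p-values, and otherwise uses a test that ignores the randomisation strata. In the simulated scenario with prognostic variables, the rule does slightly worse than never adjusting (73.8% against 75.2%) and clearly worse than a fixed model. By formula, fixed adjustment raises power from 73.8% to between 75.9% and 82.7% for R² of 0.05 to 0.20, and costs almost nothing if only an uninformative stratum is added.

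These gains rest on R² values that the documents do not give. The flag probabilities rest on assumed numbers of independent tests. Neither bias over randomisation nor type I error inflation is shown. Severity: should be fixed.

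**What to change.** - Delete the significance trigger.
- Make the primary comparison a pre-specified regression model that always includes disease stratum (HF, CLD, both), whatever the baseline table shows. Name the model before the first between-group comparison, which is due at 3 months.
- Add the prior-year admission count as a second fixed covariate if it can be extracted for all patients from the hospital records used for screening. If it cannot, use stratum alone.
- Report baseline tables descriptively, without significance tests.
- Label the unadjusted t or Mann-Whitney test, and any other adjusted model, as sensitivity analyses.

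The cost is small: a few sentences of text and no extra patients. The Mann-Whitney test, which takes no covariates, would no longer be the primary test. The admission count must be added to the dataset, and if it proved uninformative it would cost about 1 point of power.
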